## Abstract

**Introduction::**

Cardamom possesses antioxidant, anti-inflammation, and blood pressure lowering properties, which might improve endothelial function in type 2 diabetic patients. However, no study has examined the effect of cardamom on diabetic patients. The present study aimed to examine the effects of 10-week green cardamom intake on blood pressure, concentrations of inflammatory and endothelial function biomarkers in type 2 diabetes mellitus patients, and its potential mechanisms.

**Methods and Analysis Design::**

Eighty overweight or obese patients with type 2 diabetes mellitus (aged 30–60 years) will be recruited into the trial and will assign to receive either cardamom (3 g/day, 6 capsules) or placebo (rusk powder, 6 capsules) for a period of 10 weeks. Systolic blood pressure and diastolic blood pressure, asymmetric dimethylarginine, and nitric oxide will be measured. Serum inflammatory markers namely interleukin 6, tumor necrosis factor-α, high-sensitivity C-reactive protein, and factors related to endothelial function including intercellular adhesion molecule-1, vascular cell adhesion molecule 1, CD62 antigen-like family member E, and cluster of differentiation 163 will be measured at baseline and at the end of the trial. Sociodemographic, International Physical Activity Questionnaire, and three 24-hour dietary recall questionnaires will be collected for each participant.

**Ethics and dissemination::**

The study has been approved by The Ethics Committee of Tehran University of Medical Sciences (IR.TUMS.REC.1395.2700). Each participant will sign a written informed consent at the beginning of the study. At the end of the study, results will be published timely manner.

**Trial registration number::**

(http://www.irct.ir, identifier: IRCT-2016042717254N5) Date of registration: 2016-11-23

LimitationsSome patients might not cooperate till the end of the study, which will be replaced with other patients.Because of the strong aroma of cardamom the placebo group might find out that they are not taking cardamom and vice versa and this limits the study to be double blinded.Small sample size which might affect generalizability of the results.Short follow-up period (10 weeks) and dose of the cardamom supplementation (3 g/day).**Strengths**According to our knowledge and searches we have done, this is one of the first randomized controlled clinical trials to assess the effects of *Elettaria cardamomum* supplementation in patients with type 2 diabetes mellitus.The present study will provide the required base for future greater clinical trials.This is a double-blind study with the least dropout.We will place placebo capsules next to cardamom capsules so the placebo capsules will have the aroma of cardamom and by this we try to lessen the limitation of the study.We will exclude participants who are taking supplements, as well as those participating in a weight loss program, and thus will be able to exclude potential confounding by these factors.

## Introduction

1

Type 2 diabetes mellitus (T2DM) is one of the most important causes of mortality and morbidity around the world.^[1]^ The International Diabetes Federation estimates that in 2010, 285 million people of the world population suffered from diabetes and by 2030 this number will increase to 439 million people of the world population.^[2]^ The incidence of cardiovascular diseases (CVDs) is 2- to 4-fold in people with T2DM.^[3]^ CVD is the major reason of morbidity in patients with T2DM, and a cause of death in approximately 3 out of 4 diabetic patients.^[4]^ Raised blood pressure is more common in people with T2DM.^[5]^

CVD is generally attributed to the adverse effects of hyperglycemia and oxidative stress on vascular biology. Vascular endothelial cells play an important role in maintaining cardiovascular homeostasis and endothelial dysfunction causes the development of atherosclerosis. In diabetic patients, endothelial dysfunction is a consistent finding.^[6]^

Inflammation is an integral part of the atherosclerotic process. Plasma concentration of inflammatory mediators, such as tumor necrosis factor-α (TNF-α), interleukin-6 (IL-6), and C-reactive protein (CRP) are higher in obesity and patients with T2DM in which insulin resistance occurs.^[7]^ Inflammatory markers stimulate endothelial production of adhesion molecules such as intercellular adhesion molecules (ICAMs), vascular cell adhesion molecule (VCAM), and endothelial-leukocyte adhesion molecule (E-selectin). These proinflammatory cytokines have a direct effect on vascular walls, which promotes atherosclerosis and leads to impaired vascular reactivity.^[8]^

Cluster of differentiation 163 (CD163) is a macrophage-specific receptor involved in the clearance and endocytosis of hemoglobin-haptoglobin complexes.^[9]^ A high CD163 expression in macrophages is a characteristic of tissues responding to inflammation and indirectly contributes to the anti-inflammatory response. sCD163 is a biomarker for inflammation in adipose tissues and also a biomarker for the development of T2DM.^[10]^ It has been indirectly associated with anti-inflammatory and atheroprotective activity^[11]^ and is a therapeutic target.^[10]^

The exact mechanisms of endothelial dysfunction in T2DM is not known but it might be related to decreased synthesis of nitric oxide (NO) or increased inactivation of NO.^[12]^ NO has cardioprotective roles which include regulation of blood pressure and vascular tone, inhibition of platelet aggregation and leukocyte adhesion, and smooth muscle cell proliferation prevention.^[13]^ NO impairment is regarded as an early step in the development of insulin resistance, atherosclerosis, and T2DM.^[14]^ Asymmetric dimethylarginine (ADMA) is a compound found in human plasma and is endogenous inhibitor of NO synthase.^[14]^ Elevated plasma ADMA levels have been observed in patients with insulin resistance and diabetes, and have been reported to predict adverse cardiovascular events in patients with T2DM.^[15]^

It has been shown that many risk factors for CVD such as hypercholesterolaemia, obesity, and T2DM are conditions in which the activation of the sirtuins had shown to have protective effects in experimental models.^[16]^ Sirtuins are the class III histone deacetylases, which are widely distributed in the body and regulate physiopathological processes, such as inflammation and have cardioprotective effects.^[16,17]^ The best characterized and well-studied among the human sirtuins is sirtuin 1 (SIRT1) which has anti-inflammatory functions in macrophages and endothelial cells. SIRT1 interferes with the transcription factor nuclear factor kappa B (NF-κB) signaling pathway which leads to downregulation of the expression of various proinflammatory cytokines.^[18]^ The production of proinflammatory cytokines in human atherosclerotic plaques is NF-κB dependent^[19]^ and NF-κB activation leads to the expression of many proinflammatory cytokines (e.g., IL-1, IL-2, IL-6, and TNF-α), adhesion molecules (e.g., VCAM, ICAM, E-selectin), and inducible proinflammatory enzymes (cyclooxygenase-2 and inducible NO synthase), which exacerbate the inflammatory process and make it perpetual.^[20]^ The results of a study demonstrate that SIRT1 plays a fundamental role in regulating endothelial NO by activating NO synthase eNOS, which increases endothelial NO.^[21]^ SIRT1 impairs synthesis and increases metabolism of ADMA.^[22]^

There are developing evidence that shows, because of their biological properties, plant foods polyphenols, may be unique nutraceuticals and supplementary treatments for various aspects of T2DM.^[23]^ Polyphenols have been shown to activate SIRT1 either directly or indirectly in vitro and in vivo. Hence, the activation of SIRT1 by polyphenols would be beneficial in therapeutic intervention of a variety of chronic diseases.^[17]^

Seeds of cardamom (*Elettaria cardamomum*) are from the Zingiberaceae family and are used as the spice ingredient in food. Cardamom contains flavonoids like quercetin, kaempferol, luteolin, and pelargonidin.^[24]^ Key components of essential oil in cardamom [i.e., 1,8-cineol (eucalyptol); beta-pinene; geraniol] by binding to NF-κB, provides anti-inflammatory activity.^[25]^ The effect of *E cardamomum* on some of the cardiovascular risk factors in individuals with stage 1 hypertension was studied. The result showed that *E cardamom* effectively reduces blood pressure, enhances fibrinolysis, and improves antioxidant status.^[26]^

Traditional remedies and as a part of that, herbal medicines are a potential source for the development of new therapeutic medicines to be used in the treatment of various diseases.^[27]^ To the best of our knowledge, no study has yet evaluated the anti-inflammatory and vascular protection effect of cardamom in patients with T2DM. The objective of this study is to investigate the effects of green cardamom supplementation on blood pressure and endothelial function. To show the mechanism of cardamom effect, inflammatory markers, CD163, SIRT1, NO, and ADMA will be measured.

## Study design and objectives

2

A double-blind randomized clinical trial design is to be used in this study.

### Objectives

2.1

Compare the mean SBP and DBP and serum NO and ADMA between the 2 groups and within each group, before and after intervention.Compare the mean serum inflammatory factors [TNF-α, IL-6, hs-CRP, CD163] between the 2 groups and within each group, before and after intervention.Compare the mean of serum ICAM, VCAM, E-selectin, and SIRT1, between the 2 groups and within each group, before and after intervention.

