#### Sample size

2.2.2

Eighty patients with T2DM diagnosed by diabetes specialist physicians were recruited from Diabetes Research Center, Endocrinology and Metabolism Clinical Sciences Institute, Tehran University of Medical Sciences Tehran, Iran to detect a significant mean difference of hsCRP,^[28]^ 95% confidence level, and 80% power. Regarding a possible loss to follow-up, a safety margin of 20% was determined The patients were divided equally in the placebo and cardamom supplement groups. We started recruiting participants from Diabetes Research Center from November 20, 2016 to July 20, 2017 and by now we are collecting data from the questionnaires and blood sample tests. 
[figure not shown]

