#### Intervention

2.2.7

The participants will be randomly assigned into 2 groups (green cardamom powder or rusk powder) for 10 weeks. Each patient will receive 2 capsules with each meal (3 g/day) for 10 weeks. Every 5 weeks supplements taken will be checked and empty packs will be received and new packages will be delivered to patients and the number of supplements will be counted. The supplements will be given simultaneously with the usual diabetes care drugs that include maintenance of the oral antidiabetic drugs dosage. All patients receive medical nutrition therapy and physical activity enforcement at this clinic. The 24 hour dietary recall will be taken from all patients at the beginning, middle and end of intervention to be confidant of constant dietary intake. Cardamom and placebo capsules will be prepared by Traditional Medicine Research Center, Tehran, Iran. Each capsule contains 0.5 g of whole green cardamom or rusk powder. Placebo capsules will be completely similar to cardamom capsules by the means of shape, size, and color. All capsules containing placebo will be put on the same bag of the cardamom capsules to take the smell of cardamom. Participants will be asked to keep their usual lifestyle including medical nutrition therapy and physical activity level.

Voucher number of green cardamom is *E cardamomum* (L) Maton, Family: Zingiberaceae, PMP-669 which was identified by School of Pharmacy, Tehran University of Medical Sciences. Essential oil content, essential oil compounds including phenolic and flavonoid content of whole green cardamom using GC-mass and HPLC will be measured in the institute of Medicinal Plants, Shahid Beheshti University of Medical Sciences. Some polyphenolic compounds of green cardamom such as caffeic acid, gallic acid, quercetin, and luteolin, which was mentioned in the other article will be determined by HPLC.^[30]^

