#### Statistical analysis

2.2.14

The normality of the distribution of data will be assessed by using Shapiro-Wilk tests carried out on each parameter before analysis. By using “regression imputation” missing values will be replaced from a regression equation from observed data. By using intention-to-treat all randomized participants will be analyzed in their group. Independent *t* test will be used to evaluate the differences between the means of 2 independent groups with normal data and Mann-Whitney for non-normal data. In order to assess time-by-treatment interactions and time effects on all outcomes two way repeated-measures regression analysis will be used. A *P* value of <.05 will be considered as significant. All statistical analyses will be performed using SPSS version 21 (SPSS Inc, Chicago, IL).

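### Before-after change within each arm is a formal objective on a par with the randomised comparison, and the plan does not say that only the latter decides efficacy

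*Protocol article*

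**What the plan says.** Protocol article, section 2.1 (Objectives). The first objective is "Compare the mean SBP and DBP and serum NO and ADMA between the 2 groups and within each group, before and after intervention". The second (TNF-α, IL-6, hs-CRP, CD163) and the third (ICAM, VCAM, E-selectin, SIRT1) use the same construction. Neither comparison is ranked above the other. The 4 + 4 + 4 = 12 variables are the same 12 that section 2.2.10.1 lists under the primary outcome.

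Section 2.2.1 (Study design) describes a parallel, double-blind, placebo-controlled randomised trial.

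Section 2.2.7 (Intervention) says of both arms: "All patients receive medical nutrition therapy and physical activity enforcement at this clinic". It also says: "Participants will be asked to keep their usual lifestyle including medical nutrition therapy and physical activity level". Section 2.2.4 requires stable oral antidiabetic doses, and section 2.2.5 excludes patients whose diet changed in the past 3 months.

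Section 2.2.14 (Statistical analysis) plans an independent t test, with Mann-Whitney for non-normal data; the t "test will be used to evaluate the differences between the means of 2 independent groups with normal data". It adds: "In order to assess time-by-treatment interactions and time effects on all outcomes two way repeated-measures regression analysis will be used". The threshold is the same throughout: a P "value of <.05 will be considered as significant". The section names no paired test, and it does not say which result carries the efficacy conclusion.

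**The concern.** In a parallel placebo-controlled trial, only the contrast between the randomised arms isolates the capsule content. A before-after change in one arm also contains whatever else happened to those patients over 10 weeks. That includes the clinic's nutrition therapy and activity programme, the effect of being observed in a trial, and drift over time. A P value for that change says nothing specific about cardamom.

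Because the objectives give the within-arm comparison equal standing, a report that meets them would include a before-after result for each arm and each variable. This invites a conclusion of a significant change with cardamom and none with placebo. That pattern is not a test of a difference between the arms. It can arise often when both arms have changed by exactly the same amount. At stake is the error rate of any efficacy statement built on it, for all 12 primary variables.

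**Working it through.** **The plan's own figure.** Section 2.2.2 gives 80 patients for a difference in hsCRP at "95% confidence level, and 80% power" with a 20% margin for loss. The difference and SD are not in the readable text, so the 80 cannot be reproduced. Nothing below depends on it except the 40 per arm.

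**Inputs**
- n = 40 per arm (section 2.2.6). A check uses 32 per arm, since 40 × (1 − 0.20) = 32.
- Significance level 0.05 (section 2.2.14). Sidedness is not stated; two-sided is assumed.
- True before-after shift, equal in both arms because the capsule is taken as inert. This is an assumption not found in the documents: 0 to 0.8 SD of the change score.
- The arms are independent, change scores are normal, and a paired t test is applied in each arm. Section 2.2.14 names no such test. It is used here only to show what meeting the within-group objective would entail.

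**Number of comparisons implied by the objectives:** 12 variables × 2 arms = 24.

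**Formulas**
- Noncentrality: δ = shift × √n.
- Within-arm power p: the probability that a noncentral t with n − 1 degrees of freedom and noncentrality δ exceeds the two-sided 5% limit. Its part in the direction of improvement is p_up.
- P(exactly one arm significant) = 2p(1 − p). This is largest, at 50%, when p = 0.5.
- P(significant improvement with cardamom only) = p_up(1 − p).

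**Results, 40 per arm** (last two columns from unrounded p)

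| Shared shift (SD) | δ = shift × √40 | p | Exactly one arm | Cardamom only |
|---|---|---|---|---|
| 0 | 0 | 0.050 | 9.5% | 2.4% |
| 0.2 | 1.26 | 0.235 | 36% | 18% |
| 0.31 | 1.96 | 0.481 | 50% | 25% |
| 0.5 | 3.16 | 0.869 | 23% | 11% |
| 0.8 | 5.06 | 0.999 | 0.3% | 0.1% |

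Example at 0.2 SD: 2 × 0.235 × 0.765 = 0.36. At zero shift: p_up(1 − p) = 0.025 × 0.95 = 0.024.

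**Results, 32 per arm.** Exactly one arm: 9.5% at 0, 31% at 0.2 SD, 50% at 0.35 SD, 34% at 0.5 SD and 1.5% at 0.8 SD. Cardamom only: 2.4%, 16%, 25%, 17% and 0.8%.

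**Comparator.** In the between-group test a shared shift cancels. A simulation of 50,000 trials per setting with 40 per arm gave two-sided rejection rates of 4.97%, 5.03%, 4.89% and 4.97% at shifts of 0, 0.2, 0.31 and 0.5 SD. The like-for-like figure for the cardamom-only column is half of 5%, about 2.5%. The same simulation gave 9.5%, 36%, 50% and 23% for exactly one arm, which agrees with the formula.

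**The case against.** The strongest reply is that the analysis section does not do what the objectives suggest. It names a between-group test and a time-by-treatment interaction, both valid, and no paired test. In a two-way model the time effect is normally one main effect pooled over the arms. It gives no separate P value per arm and cannot by itself yield a contrast of significant against non-significant. On this view the objectives merely describe the between and within factors of that model. This stands in part. A reader might infer that the plan lacks a proper randomised comparison, or that it schedules 24 extra tests. Neither is supported: the 24 follow from the objectives alone. What remains is that the objectives ask explicitly for a comparison within each group, which the pooled time effect does not answer, and that no sentence subordinates it.

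A reader might also infer that within-arm significance will be taken as efficacy. The documents do not say so. They only leave it open.

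The third reply concerns the shared shift. Nutrition therapy and activity enforcement read as continuing care. Patients are to keep their usual lifestyle, recent diet change is an exclusion, drug doses are to be stable, and three dietary recalls check that intake is constant. Entry is by glucose, HbA1c and BMI rather than by blood pressure or the markers, so regression to the mean is a weak mechanism here. All this stands. The shift may be small, and the documents give no evidence that it lies near the worst case. At zero shift the cardamom-only rate is 2.4%, no worse than the valid test in that direction.

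**Conclusion.** The point holds in limited form. The objectives give a comparison that cannot isolate cardamom the same rank as the one that can, for all 12 primary variables. Section 2.2.14 tests time effects at the same threshold without saying that only the randomised contrast decides efficacy. The valid contrasts are planned, so this is an extra objective that should be demoted, not a gap in the design.

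If within-arm results were used to judge efficacy, the error per variable would range from negligible to severe with the shared shift. For an inert capsule and 40 per arm, cardamom-only improvement runs from 0.1% to 25%, against about 2.5% for the between-group test. The 50% and 25% figures are the maximum over an assumed range, not an expected value. They rest on equal true shifts, independent arms, normal change scores and two-sided paired tests at 0.05. The change is worth making because the objectives as worded are unsound whatever the shift, and the remedy is almost free.

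**What to change.** 1. Section 2.1: reword each objective to the between-group difference in change from baseline to week 10 for the listed variables, and remove the within-group comparison from the objectives.
2. Section 2.2.14: report within-arm change as description only, as mean change with 95% confidence interval and no P value.
3. Section 2.2.14: add a sentence such as: *Conclusions on efficacy rest only on the between-group contrast (time-by-treatment interaction); time effects and changes within an arm are descriptive and will not be used to claim an effect of cardamom.*

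The cost is wording in two sections, with no new patients, visits or measurements. The downside is that within-arm P values are no longer reported as results. As section 2.2.2 says that data are already being collected, the change should be dated and made before the A and B packages are decoded.

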### Methods and analysis design

2.2

#### Study design

2.2.1

The study consisted of a parallel, double-blind randomized, placebo controlled clinical trial with treatment and control groups. A flow chart of the study protocol is shown in Figure 1.

**Figure 1 F1:**
[figure not shown]
Participants flow diagram.

#### Sample size

2.2.2

Eighty patients with T2DM diagnosed by diabetes specialist physicians were recruited from Diabetes Research Center, Endocrinology and Metabolism Clinical Sciences Institute, Tehran University of Medical Sciences Tehran, Iran to detect a significant mean difference of hsCRP,^[28]^ 95% confidence level, and 80% power. Regarding a possible loss to follow-up, a safety margin of 20% was determined The patients were divided equally in the placebo and cardamom supplement groups. We started recruiting participants from Diabetes Research Center from November 20, 2016 to July 20, 2017 and by now we are collecting data from the questionnaires and blood sample tests. 
[figure not shown]

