#### Randomization

2.2.6

The participants will be randomly assigned into 2 groups green cardamom powder (n = 40) or rusk powder (n = 40). The permuted block randomization will be used in this study. Stratified randomization will be used to control BMI and gender distribution, those will be 25–29.9/30–34.9 kg/m^2^ for BMI and for gender, respectively. Randomization will be performed by an assistant and the intervention allocation will be blinded as A and B packages for investigators and patients.

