##### Primary outcome

2.2.10.1

Primary outcome of this trial includes changes in SBP and DBP, NO, and ADMA. Changes in serum inflammatory markers Il-6, TNF-α, hsCRP, and changes in factors related to endothelial function serum ICAM, VCAM, E-selectin, CD163, and SIRT1.

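### The 80% power covers hsCRP only, one of 12 variables listed as primary; none is stated for the first-named outcomes (SBP, DBP, NO, ADMA)

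*Protocol article*

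**What the plan says.** All references are to the protocol article.

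- **Sample size (2.2.2):** the 80 patients were chosen "to detect a significant mean difference of hsCRP", with "95% confidence level, and 80% power". On attrition: "Regarding a possible loss to follow-up, a safety margin of 20% was determined". This is the only power statement in the readable text. An image after the paragraph is not shown.
- **Introduction:** "The objective of this study is to investigate the effects of green cardamom supplementation on blood pressure and endothelial function". The next sentence reads: "To show the mechanism of cardamom effect, inflammatory markers, CD163, SIRT1, NO, and ADMA will be measured".
- **Objectives (2.1):** blood pressure, NO and ADMA form the first objective. hsCRP appears in the second, with the other inflammatory factors.
- **Primary outcome (2.2.10.1):** "Primary outcome of this trial includes changes in SBP and DBP, NO, and ADMA". A second, verbless sentence under the same heading adds IL-6, TNF-α, hsCRP, ICAM, VCAM, E-selectin, CD163 and SIRT1. That makes 4 + 8 = 12 variables.
- **Secondary outcomes (2.2.10.2):** weight, BMI and waist circumference only.
- **Statistical analysis (2.2.14):** between-group t test (Mann-Whitney if non-normal) and a two-way repeated-measures analysis. A P "value of <.05 will be considered as significant", with no division of alpha between outcomes.

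**The concern.** A power statement tells the reader how likely the trial is to find the effect it is mainly looking for. Here it is tied to a variable that is neither named first among the primary outcomes nor part of the first objective. For blood pressure, NO and ADMA the article gives neither a power nor a detectable difference.

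Interpretation is what is at stake. If blood pressure turns out non-significant, a reader may take it as a negative result from a trial with 80% power, although that figure was never worked out for blood pressure. With 12 primary variables and one power calculation, it is also unclear which result decides whether the trial succeeded.

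**Working it through.** **Inputs from the article.** 80 patients, 40 per arm (Randomization, 2.2.6); 5% level; 80% power; 20% margin for loss; independent t test. Sidedness is not stated, so two-sided is assumed.

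**1. The plan's own figure.** The readable text gives no hsCRP difference or SD, so 80 cannot be derived forwards. Working backwards, 32 / (1 − 0.20) = 40 per arm, so 32 evaluable patients per arm fit the stated margin. So do 33 per arm with a 20% increase: 33 × 1.2 = 39.6, rounded up to 40. The sample size is consistent with the stated alpha, power and margin, but not independently verified.

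**2. Detectable difference at 80% power.** Normal approximation: d = (1.960 + 0.842) × √(2/n).

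| n per arm | Normal | Exact noncentral t |
|---|---|---|
| 40 | 0.626 SD | 0.634 SD |
| 32 | 0.700 SD | 0.711 SD |

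These depend only on n, so they hold equally for hsCRP, blood pressure, NO and ADMA.

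**3. What this could mean for systolic pressure.** The article gives no SD and no target difference. As assumptions, take SDs of 10 to 18 mmHg and a true effect of 5 mmHg. The standardised effect is d = 5/SD and the noncentrality is d × √(n/2), with 2n − 2 degrees of freedom.

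| Assumed SD (mmHg) | d | Power, 32 per arm | Power, 40 per arm |
|---|---|---|---|
| 10 | 0.500 | 50% | 60% |
| 12 | 0.417 | 37.5% | 45% |
| 15 | 0.333 | 26% | 31% |
| 18 | 0.278 | 19% | 23% |

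**4. Gain from baseline adjustment.** Adjusting for the baseline value multiplies the detectable difference by √(1 − r²), where r is the baseline-to-final correlation. With r assumed to be 0.5 to 0.7:

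- 40 per arm: 0.634 × 0.866 = 0.55 SD, down to 0.634 × 0.714 = 0.45 SD.
- 32 per arm: 0.711 × 0.866 = 0.62 SD, down to 0.711 × 0.714 = 0.51 SD.

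**The case against.** The strongest reply is that the trial is powered on one of its own primary outcomes. hsCRP stands under the Primary outcome heading and is not among the secondary outcomes. Inflammation is also part of the stated question: the Abstract's aim includes inflammatory biomarkers, and the Discussion gives the aim as inflammation and endothelial function without mentioning blood pressure. All of this stands. It means the 80% does refer to a listed primary outcome, but it does not extend that figure to the other 11.

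A reader might infer three stronger criticisms, which the article does not support:

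- **That hsCRP is only a mechanism marker.** The Introduction puts inflammatory markers in its mechanism sentence, but NO and ADMA are in the same sentence. That label does not separate hsCRP from the outcomes named first, although blood pressure is outside the list.
- **That the 80% fails even for hsCRP because 12 outcomes share the 5%.** Power of about 46% (0.05/12, 32 per arm) would follow from a Bonferroni rule, but the plan contains none. Each test is at 5%, so the hsCRP test keeps its nominal power. Twelve tests at 5% raise a type I error question, which is separate.
- **That the design could see only very large blood pressure effects.** No SD or relevant difference is given, so this cannot be judged. Moreover, 32 per arm is the pessimistic case: the Limitations say that patients who stop will be replaced, and 2.2.14 plans to analyse everyone randomised, with imputation. Baseline adjustment would also lower the detectable difference.

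The absent hsCRP difference and SD are not held against the plan, because the unseen image may contain them.

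**Conclusion.** The mismatch is real and should be corrected. The 80% is a single-test figure for one of 12 variables listed as primary, and for none of the four named first. With the planned numbers, an unadjusted two-sided t test reaches 80% power at 0.63 SD (40 per arm) to 0.71 SD (32 per arm) for any outcome.

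The detectable difference needs only the sample size, the 5% level, two-sided testing and the unadjusted t test. The blood pressure powers of 19% to 60% rest further on the assumed 5 mmHg effect and SDs of 10 to 18 mmHg. They show that 80% cannot be presumed for blood pressure; they do not establish that the trial is too small.

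**What to change.** Make these changes before unblinding:

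1. **Name one primary outcome in 2.2.10.1 and make 2.2.2 describe it.** If it is hsCRP, keep the 80% and label the other 11 as secondary. If it is blood pressure, specify which measure and replace the 80% with the power or detectable difference for it.
2. **Record the choice as a dated change, with the reason.** Section 2.2.2 gives recruitment as ending on July 20, 2017, with data being collected, so any choice now comes after enrolment. A reader must be able to see that it was made without knowledge of results by arm.
3. **Analyse the primary outcome with adjustment for its baseline value.** Blood markers are already measured at baseline and week 10, and the outcomes are defined as changes. Under the assumed correlations, the detectable difference becomes about 0.45 to 0.62 SD.
4. **State in 2.2.2 that the 80% covers hsCRP only,** and give the detectable difference for the other outcomes (0.63 to 0.71 SD unadjusted).
5. **Interpret a non-significant blood pressure result by its confidence interval:** it is inconclusive unless the interval excludes a relevant effect.

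This needs no additional patients or measurements. The cost is a less favourable power statement, fewer outcomes with confirmatory status, and a primary outcome visibly settled after enrolment, which the dated record mitigates but does not remove.
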